### Harms

There are standard routines to follow-up patient safety at each PHCC. Participating PHCCs have the possibility to report potential harms related to the trial to the study team. Risks to healthcare professionals and patients associated with the trial are anticipated to be minimal, given the educational nature of the intervention and its delivery at the PHCC level. While the study promotes guideline-concordant opioid prescribing, it does not advocate indiscriminate reductions, recognising the essential role of opioids in pain management. To mitigate the theoretical risk of overly restrictive prescribing or abrupt discontinuation, the intervention emphasises adherence to clinical guidelines and safe deprescribing practices.

### Participant timeline

The duration of the intervention was 12 months from the date of the seminar visit, which was defined as the baseline date. Data on opioid prescriptions will be collected over a five-year period: two preintervention years prior to baseline and three years after baseline (figure 1). PHCC enrolment began in spring 2023, and seminar visits were conducted between June 2023 and February 2024. The final data extraction is planned for 36 months after the final seminar visit.

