### Randomisation and blinding

#### Allocation to the intervention or the active control group

Consenting PHCCs will be enrolled on a rolling basis and randomised in a 1:1 parallel design to either the intervention or active control group. Randomisation will be pairwise, stratified by PHCC size, using computer-generated random numbers. PHCCs unmatched due to uneven numbers at a given time point will be carried forward to the next randomisation date, and any remaining unmatched PHCCs will be randomly allocated to either group.

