#### Assignment of the GP delivering the intervention

At each randomisation time point, intervention PHCCs will also be randomised to one of two GPs who will conduct the seminar visit. Uneven allocation ratios (eg, 3:2) may be used due to differences in GP availability during the study period.

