#### Assignment of baseline dates

PHCCs in the active control and observational reference groups will be assigned baseline dates to match intervention PHCC seminar visit dates. This ensures temporal alignment across groups and allows the leaflet to be sent to active control PHCCs on the same date as their corresponding intervention PHCCs.

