#### Blinding

This is a pragmatic trial in which intervention assignment is known to both PHCCs and the study team. The statistician responsible for randomisation and outcome analyses will be blinded to PHCC names and the identity of the GP delivering the intervention. Analyses will be conducted using deidentified PHCC codes.

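### The baseline window runs past open-label randomisation to the seminar date, so a reaction to known allocation can enter both the change score and the covariate

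*Protocol article*

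**What the plan says.** All of the following is in the Protocol article.

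- **Time zero.** Participant timeline says that the intervention lasts "12 months from the date of the seminar visit, which was defined as the baseline date".
- **Other groups.** Assignment of baseline dates says: "PHCCs in the active control and observational reference groups will be assigned baseline dates to match intervention PHCC seminar visit dates". It adds that this "allows the leaflet to be sent to active control PHCCs on the same date as their corresponding intervention PHCCs".
- **Order of events.** Under allocation: "Consenting PHCCs will be enrolled on a rolling basis and randomised in a 1:1 parallel design". Under assignment of the GP: "At each randomisation time point, intervention PHCCs will also be randomised to one of two GPs who will conduct the seminar visit". The seminar therefore follows randomisation.
- **Openness.** Blinding states that "intervention assignment is known to both PHCCs and the study team".
- **Calendar.** "PHCC enrolment began in spring 2023, and seminar visits were conducted between June 2023 and February 2024". The interval from randomisation to seminar is not given for any centre.
- **Use of the baseline.** Under Analyses of primary and secondary outcomes, the windows are 12 months before and 12 or 24 months after the intervention. Each centre's change in DDDs per patient-month is regressed on group, with baseline prescribing and the matching variables in the model.

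**The concern.** A baseline covariate is safe to adjust for because allocation cannot have influenced it. Here the window closes at the seminar, after allocation has been made and disclosed, so its last months are post-randomisation. An intervention centre knows that it has agreed to a trial about its opioid prescribing, and that a seminar is coming which compares its figures with those of nearby centres. It may begin to prescribe more cautiously before the visit. A control centre waiting for an emailed leaflet has less reason to do so.

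Any such difference lowers the intervention arm's baseline. The analysis then subtracts it in the change score and adjusts for it in the regression. Matched dates give both arms the same calendar window, but they do not remove a reaction that differs by arm. At stake is an understated primary contrast and some loss of power. An early reduction confined to control centres would act in the opposite direction.

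**Working it through.** **The plan's own figure.** Sample size gives 24 centres per group for a 10% change, with 80% power, two-sided 5% and one covariate with r = 0.39. The SD of the change score is not stated, so 24 cannot be reproduced forwards. Solved backwards with the normal approximation:

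- residual SD = 10 × √(24/2) / (1.960 + 0.842) = 34.64 / 2.802 = 12.36% of mean prescribing;
- SD of change = 12.36 / √(1 − 0.39²) = 12.36 / 0.921 = 13.4% (13.1% with a t distribution on 45 df).

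This neither confirms nor refutes 24. It only sets the scale for the power figures below.

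**Attenuation.** Three quantities are needed, and the documents give none of them:

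- *g*: months from randomisation to seminar;
- *a*: share of the full effect already present during those months, in the intervention arm only;
- *b*: slope of follow-up on baseline prescribing. *b* = 1 is the pure change score. The stated r = 0.39 does not yield *b* without the SD of baseline prescribing.

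With true effect Δ, the intervention arm's 12-month baseline shifts by Δ × a × g/12. Regressing the change on group and baseline gives the same group coefficient as regressing follow-up on group and baseline, so the expected contrast is

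Δ × (1 − b × a × g/12).

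The standard error is 12.36 × √(2/24) = 3.57, and power ≈ Φ(contrast/3.57 − 1.96).

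| g (months) | a | b | Contrast (true 10%) | Power |
|---|---|---|---|---|
| any | 0 | any | 10% | 80% |
| 3 | 0.10 | 1 | 9.75% | 78% |
| 3 | 0.25 | 1 | 9.4% | 75% |
| 3 | 0.50 | 1 | 8.75% | 69% |
| 6 | 0.10 | 1 | 9.5% | 76% |
| 6 | 0.25 | 1 | 8.75% | 69% |
| 6 | 0.50 | 1 | 7.5% | 56% |
| 3 | 0.25 | 0.5 | 9.7% | 77.5% |
| 6 | 0.50 | 0.5 | 8.75% | 69% |

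Worked example, second 3-month row: 10 × (1 − 0.25 × 3/12) = 9.375; 9.375/3.57 − 1.96 = 0.67; Φ(0.67) ≈ 0.75.

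The planned model adjusts for baseline, so the *b* = 1 rows are the upper end of the attenuation for any slope up to 1.

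**Can the window be moved?** Extraction covers two years before the seminar date. A 12-month window ending at randomisation needs 12 + g months. Taking enrolment from March 2023 at the earliest and the last seminar in February 2024, g is at most about 11, so at most about 23 of the 24 months are needed.

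**The case against.** The defence of the present definition is reasonable. The seminar, written materials, feedback and leaflet all start at or after baseline, so it marks the moment delivery begins and is aligned across arms. A reader might infer that the baseline absorbs the treatment effect itself. The documents do not support that: nothing is delivered in the gap, and only anticipation can enter. A reaction to consent or enrolment that is common to both arms cancels. The article does not say when individual prescribers learn the allocation. Because randomisation was rolling, the span from spring 2023 to February 2024 says little about any one centre's gap. Bias from early reduction in intervention centres is towards no effect, so it would not create a false positive. All of this stands and limits the likely size, but it does not make a post-randomisation window a pre-randomisation one.

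Two further inferences are tempting, and neither is supported.

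- *An intervention centre without a seminar has no analysable data, or drops out together with its control.* The outcome comes from a regional register that covers every centre whether or not a seminar takes place. No sentence makes a seminar a condition for analysis, and nothing suggests that one was missed. A substitute date, or a statement that centres are analysed as randomised, may properly sit in an analysis plan that is not shown.
- *A leftover control cannot be dated*, because "any remaining unmatched PHCCs will be randomly allocated to either group". Reference centres belong to no randomised pair and still receive assigned dates, so the same mechanism can serve an unmatched control.

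**Conclusion.** The point holds in a limited form. The article fixes a baseline window that includes open-label, post-randomisation months, and that value enters the primary model twice. Arm-specific anticipation can therefore bias the contrast, towards no effect if intervention centres reduce prescribing early.

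The size cannot be known from the documents. It is nil without anticipation and small for a short gap with weak anticipation. It becomes material only with a long gap and strong anticipation, and it is smaller in every case if the baseline slope is below 1. The gap, the anticipated share and the slope are all assumptions, and the power figures also rest on an SD solved backwards from 24 per group. The reason to act is that the exposure can be removed by design at little cost, not that serious bias has been shown.

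**What to change.** For the primary analysis, end the 12-month baseline window at the pair's randomisation date in both arms; a centre randomised alone uses its own date. Keep the shared seminar or leaflet date as the start of the 12- and 24-month follow-up. Retain the seminar-date baseline as a sensitivity analysis, and report the interval from randomisation to seminar so that readers can judge how much the choice matters. Fix this before outcome data are analysed.

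The cost is wording and a date variable. Randomisation dates should be on file, and the planned two-year pre-seminar extraction already covers the earlier window. The statistical price is a short period between randomisation and seminar that is used in neither window, and a slightly lower correlation between baseline and follow-up, hence slightly less precision from the adjustment.

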**Figure 1 F1:**
[figure not shown]
Schema of the *Smarta Val* pragmatic cluster randomised trial and study timepoints.

### Sample size

The outcome will be measured at the cluster level, using aggregated prescribing data for all registered patients at each PHCC. It was estimated that a minimum of 24 PHCCs per group were required to detect a 10% change in opioid prescribing between intervention and active control clinics. The calculation was based on a cluster-level regression analysis comparing change scores between groups, adjusted for baseline prescribing. Assumptions included 80% power, a two-sided significance level of 5%, and one covariate correlated with the outcome (r=0.39).

### Randomisation and blinding

#### Allocation to the intervention or the active control group

Consenting PHCCs will be enrolled on a rolling basis and randomised in a 1:1 parallel design to either the intervention or active control group. Randomisation will be pairwise, stratified by PHCC size, using computer-generated random numbers. PHCCs unmatched due to uneven numbers at a given time point will be carried forward to the next randomisation date, and any remaining unmatched PHCCs will be randomly allocated to either group.

#### Assignment of the GP delivering the intervention

At each randomisation time point, intervention PHCCs will also be randomised to one of two GPs who will conduct the seminar visit. Uneven allocation ratios (eg, 3:2) may be used due to differences in GP availability during the study period.

#### Assignment of baseline dates

PHCCs in the active control and observational reference groups will be assigned baseline dates to match intervention PHCC seminar visit dates. This ensures temporal alignment across groups and allows the leaflet to be sent to active control PHCCs on the same date as their corresponding intervention PHCCs.

#### Blinding

This is a pragmatic trial in which intervention assignment is known to both PHCCs and the study team. The statistician responsible for randomisation and outcome analyses will be blinded to PHCC names and the identity of the GP delivering the intervention. Analyses will be conducted using deidentified PHCC codes.

#### Data collection and management

Data for this study will be obtained from three sources: regional healthcare databases, questionnaires administered to PHCC managers and an intervention delivery form completed by study coordinators.

#### Regional healthcare databases

VAL is the name of the centralised data warehouse for monitoring healthcare utilisation in Region Stockholm.^37^ The regional healthcare databases in VAL include comprehensive healthcare records on all residents, including the PHCCs at which patients are registered, inpatient and outpatient visits, and prescriptions.

Data on the study population will be extracted from the databases for the five-year study period. At the level of the PHCC, variables include ownership type (public or private sector) and sociodemographic classification. Patient-level variables include data on PHCC registration, sociodemographic characteristics (eg, age, sex, Mosaic socioeconomic classification), and healthcare utilisation (eg, prescriptions, diagnoses and visit types).

Opioid prescribing will be quantified using dispensed DDDs, a WHO standard measure based on the assumed average maintenance dose for a drug’s main indication in adults,^38^ which is available in VAL. Key data to assess study outcomes include PHCC registration, prescribing PHCC, opioid ATC code, dispensation date, DDD per package, and the number of packages dispensed. Variables that will be used in the analysis of primary and secondary outcomes are listed in table 3. Additional variables such as migration events and date of death may also be included.

**Table 3 T3:** Variables and descriptions from the regional healthcare databases (VAL) used to assess primary and secondary outcomes

Variable	Description
Registered patients per PHCC	Calculated from the number of individual registered patients at a PHCC each calendar month
Size of PHCC	Classification of PHCC size calculated from the number of registered patients: small (<5500), medium (5500–8500) or large (>8500)
PHCC registration	PHCC name, where a patient is registered each calendar month
ATC code	Seven-digit ATC code identifying the opioid substance prescribed
Prescribing PHCC	Name of the prescribing PHCC
Dispensation date	Date opioid was dispensed
Package DDD	DDDs per package dispensed
Number of packages	Number of packages dispensed

ATC, Anatomical Therapeutic Chemical; DDD, defined daily dose; PHCC, primary healthcare centre.

### Questionnaires

Questionnaires will be administered to PHCC managers in the intervention and active control groups at baseline (online supplemental table 1) and at 12-month follow-up (online supplemental tables 2,3) to assess contextual and intervention delivery-related factors.

Baseline questionnaires include the number and types of healthcare professionals (eg, GPs, nurses and psychologists/psychotherapists) employed by contract type, average number of registered patients per GP and rating of opioid prescribing routines at the PHCC. Follow-up questionnaires include the same question about rating of prescribing routines, but also ask about changes in prescribing routines, their experience of the intervention, use of study materials, personnel changes and involvement in non-intervention projects related to pain management or opioid prescription (eg, internships, specialist training and quality improvement projects).

### Intervention delivery form

The intervention delivery form will be filled out by one of two research coordinators at each seminar visit at baseline for intervention group PHCCs (online supplemental figure 3). It includes fields on attendance to assess reach, variables regarding the delivery of intervention, components to assess dose delivered and received, items to assess intervention fidelity and a section for observations.

### Data management

Data from questionnaires and forms will be entered into a secure electronic database. Deidentified data from the VAL regional healthcare databases will be delivered directly from the Centre for Health Data, Region Stockholm. All data will be stored and managed in accordance with Region Stockholm regulations and the EU General Data Protection Regulation. Only authorised study personnel will have access.

### Statistical methods

#### Descriptive analyses

Descriptive statistics will be used to summarise the characteristics of PHCCs and patient populations. Continuous variables will be presented as means with SDs, and categorical variables as frequencies with percentages. Baseline questionnaire data for the intervention and active control groups will also be summarised to highlight any differences between the groups. Open-ended responses will be analysed using qualitative methods.

#### Analyses of primary and secondary outcomes

Analyses of primary and secondary outcomes will be conducted at the PHCC level, with comparisons made between the intervention group and the active control group, as well as between the intervention group and the observational reference group. Patients registered at the PHCCs at any point during the 12 months before and 12 or 24 months after the intervention will be included in the analyses.

The number of dispensed DDDs of opioids and the number of patient-months (ie, the number of months during which patients are registered at a given PHCC) will be summarised for each PHCC. The change in DDDs per patient-month from baseline to follow-up will be calculated for each PHCC.

The difference in change between the groups will be estimated using linear regression, with baseline prescribing (DDDs per patient-month) and the matching variables accounted for in the analysis. Cluster effects at the patient level will not be adjusted for, as the unit of analysis is the PHCC. The assumption of normality will be assessed by inspecting the model residuals. Estimated effect sizes will be reported with p values (two-sided, α=0.05) and 95% CIs. A sensitivity analysis using morphine milligram equivalents may be used as a complement to DDDs to account for potency differences between opioid substances. Exploratory subgroup analyses based on characteristics of patients at participating PHCCs may also be conducted.

Cluster-level analyses will be based on register data from regional healthcare databases, which have full coverage of prescription data; missing data are not anticipated.

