### Eligibility and recruitment

The following steps will be used to identify eligible PHCCs:

Identify PHCCs in Stockholm County with more than 3000 registered adult patients (≥18 years) as of December 2022 (n=207).Among these, select PHCCs in the top 50% of opioid prescription volume, measured using defined daily dose (DDD) per registered patient for all opioids classified under Anatomical Therapeutic Chemical (ATC) code N02A. For these high-prescribing PHCCs (n=105), the prescribing range corresponds to 0.137–0.491 DDDs per registered patient.Send study invitations via email to managers of PHCCs meeting the above criteria.

Research coordinators will confirm eligibility with interested PHCC managers through verbal or written contact prior to obtaining written informed consent (online supplemental figure 1). Detailed eligibility criteria are presented in table 1.

**Table 1 T1:** Eligibility criteria for the *Smarta Val* trial

Category	Criteria
Inclusion	Holds a primary care contract with Region Stockholm and is thus connected to regional healthcare databases (VAL) Employs at least two full-time general practitioners
Exclusion	Has been in operation for less than 12 months

Recruitment strategies include contacting PHCC managers through up to three follow-up emails and three phone calls.

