### Observational reference group

PHCCs in the observational reference group are not randomised, receive no study intervention and continue with usual care practices.

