## Discussion

This cluster randomised trial is the first to evaluate an education-based intervention to improve opioid prescribing practices in Swedish primary care. The intervention incorporates components that have been shown to be effective in prior research, including an educational seminar, written materials, and audit and feedback, and is designed to be time-efficient and scalable for routine care.

Use of regional healthcare databases enables longitudinal tracking of opioid prescribing over multiple years. The inclusion of intervention, active control and observational reference groups supports robust evaluation of intervention effects while accounting for secular trends. The extended follow-up and examination of intervention delivery may offer insights into long-term effects and implementation in routine practice.

The pragmatic design enables assessment of real-world opioid prescribing in primary care. However, this design involves less control over intervention fidelity, higher variability in implementation across PHCCs and potential contamination between PHCCs, which may affect internal validity. Additionally, the trial is conducted among high-prescribing PHCCs that opted to participate, which may limit generalisability. However, the inclusion of both an active control group and an observational reference group supports broader contextual interpretation and strengthens external validity.

Improving adherence to clinical guidelines in primary care has the potential to reduce inappropriate opioid prescription and associated harms. Given the central role of primary care in managing chronic pain and initiating opioid therapy, interventions targeting this clinical setting are particularly relevant. Findings from this study may contribute to the knowledge base on behavioural interventions and inform future strategies to support safe and evidence-based prescribing of opioids.

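### Intervention-versus-reference contrast: ordinary regression standard errors are exposed if the reference centres are many and lower-prescribing; naming HC3 errors for it is a cheap safeguard (minor)

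*Protocol article*

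**What the plan says.** In the protocol article, under Analyses of primary and secondary outcomes, the intervention group is compared with the active control group "as well as between the intervention group and the observational reference group". One model serves both comparisons: "The difference in change between the groups will be estimated using linear regression". It adjusts for each PHCC's starting prescribing level and for the variables used in matching. On assumptions the section says: "The assumption of normality will be assessed by inspecting the model residuals". On reporting: "Estimated effect sizes will be reported with p values (two-sided, α=0.05) and 95% CIs". It mentions neither unequal variances nor the type of standard error.

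Eligibility and recruitment starts from 207 PHCCs of sufficient size and invites the upper half by prescribing volume, 105 PHCCs, for which "the prescribing range corresponds to 0.137–0.491 DDDs per registered patient". The reference group is described differently: "PHCCs in the observational reference group are not randomised, receive no study intervention and continue with usual care practices". The article gives no prescribing criterion and no number for it.

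The Abstract gives the reference group a contextual role. The Objective nevertheless includes the comparison with it, and the strengths and limitations box credits the three-group design with separating intervention effects from secular trends.

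**The concern.** All intervention PHCCs come from the upper half of prescribing. As far as the article shows, reference PHCCs may come from anywhere. The outcome is an absolute change in defined daily doses (DDDs) per patient-month, built from summed dispensed packages, and the spread of such a quantity often grows with its level. Adjusting for baseline prescribing corrects the mean for level but does nothing about the variance.

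Ordinary least squares (OLS) estimates a single residual variance. If a small, more variable group is set against a large, less variable one, that single variance is dominated by the large group and is too low for the small one. The standard error of the group difference is then understated, the 95% CI is too narrow and the test rejects too often. A normality check on residuals is not aimed at this. The error would be additional to any confounding from the lack of randomisation, and it would reach the p values and intervals planned for this contrast.

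**Working it through.** **The plan's own figure.** The Sample size section gives 24 PHCCs per group for a 10% change, 80% power, two-sided 5% and r = 0.39. With n = 2(1 − r²)(1.960 + 0.842)²(SD/δ)², this is 24 = 2 × 0.848 × 7.849 × (SD/δ)², so SD/δ = 1.343, or an SD of about 13.4% of mean prescribing if δ = 10%. No SD is stated, so the 24 cannot be checked independently. It does not drive this point, which depends on ratios of SDs and on group sizes.

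**Inputs.** From the documents: n₁ = 24 intervention PHCCs; 207 PHCCs passing the size screen; 105 high prescribers. If exactly 48 are randomised, the possible reference sets are 105 − 48 = 57 eligible non-randomised PHCCs, 207 − 105 = 102 below the screen, and 207 − 48 = 159 in all. Assumed, because the documents do not say: which set is used, and the ratio k of the intervention SD to the reference SD.

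**Formula.** With the reference SD set to 1, the pooled variance is s² = [(n₁ − 1)k² + (n₂ − 1)]/(n₁ + n₂ − 2). The ratio of reported to true SE is R = √{s²(1/n₁ + 1/n₂) / (k²/n₁ + 1/n₂)}. Type I error is about 2Φ(−t₀.₉₇₅ R).

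**Worked case, 24 versus 159 with k = 1.5.**
- s² = (23 × 2.25 + 158)/181 = 1.159.
- R² = 1.159 × (1/24 + 1/159) / (2.25/24 + 1/159) = 0.0556/0.1000 = 0.556, so R = 0.745.
- The SE is 25% too small and type I error is about 14.1%.

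**Same formula over a range of k.**

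| Reference n₂ | k = 0.8 | k = 1 | k = 1.25 | k = 1.5 | k = 2 |
|---|---|---|---|---|---|
| 57 | 2.9% | 4.7% | 6.9% | 9.0% | 12.2% |
| 102 | 2.3% | 4.8% | 8.5% | 12.1% | 18.2% |
| 159 | 2.0% | 4.8% | 9.4% | 14.1% | 22.2% |

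With 24 versus 24, R = 1 for every k.

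**Simulation of the planned regression.** Change was regressed on group and baseline with no true effect, 4,000 runs per cell. Baselines were lognormal with median 0.137 and log-SD 0.4 or 0.5. Residual variance was proportional to baseline or to its square. All of this is assumed. Ranges are over the four combinations.

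| Reference set | OLS type I error | HC3 type I error |
|---|---|---|
| 57 eligible, not randomised | 4.9–5.0% | 4.4–4.8% |
| 24 drawn from the 159 | 5.8–8.4% | 4.3–5.6% |
| All 159 | 9.3–15.3% | 4.8–5.5% |
| Only the 102 below the screen | 8.6–19.2% | 4.6–6.0% |

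For all 159, the simulated SD ratio was about 1.20–1.44. Equal numbers do not protect fully in the second row, because group and baseline are correlated there.

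A repeat with PHCC size added to the model gave OLS rates of 9.7–14.4% (all 159) and 11.0–16.4% (the 102) when noise rises with level, against 4.9–5.4% with HC3. If noise does not depend on level, the OLS rate is about 5% throughout.

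**The case against.** The article says linear regression. It does not say equal variances. The choice of variance estimator is commonly left to the analysis plan, which is not shown, and a condensed article may also omit how reference PHCCs were chosen. This stands: the text contains no false statement or contradiction, and its silence on standard errors is not itself an error.

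A reader might infer that the reference group includes low prescribers, because the Discussion first concedes that "the trial is conducted among high-prescribing PHCCs that opted to participate, which may limit generalisability" and then points to the reference group. The inference fails. The same passage credits the active control group too, and every PHCC in that group passed the screen. The strengths and limitations box makes a similar argument about PHCCs that opted in, which fits a reference group of eligible non-participants equally well.

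A reader might also infer that the test for this contrast runs at 10–17%. The documents do not support that either. A figure as high as 17% arises in simulations where the reference consists solely of the 102 PHCCs below the screen, and no section suggests such a group. The documents give no SD and no relation between variance and level. If the reference group is the more variable one (k = 0.8), the test is conservative, at 2.0–2.9% in the formula.

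Finally, the contrast is supporting: the sample size is set for intervention versus active control only, and confounding is the larger threat to a non-randomised comparison. This limits the weight of the point. It does not remove it, since the comparison stands in the Objective and is to carry p values and 95% CIs.

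**Conclusion.** The point holds conditionally and is minor. The stated method is safe for the randomised contrast, where the groups are of equal size and pass the same screen. For the reference contrast, its validity depends on a reference group whose size and selection the article does not give.

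If that group is large and lower-prescribing and variance rises with level, type I error is about 10–14% with all 159 other PHCCs and 6–8% with 24 drawn from them. With the 57 eligible non-randomised PHCCs, or with level-independent noise, it stays at about 5%. These rates illustrate the stated assumptions and are not properties of the trial. HC3 keeps the rate near 5% in all the cases simulated, so it is worth specifying without first settling which case applies.

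**What to change.** Under Analyses of primary and secondary outcomes, specify heteroscedasticity-robust (HC3) standard errors, with the matching p values and 95% CIs, for the intervention-versus-reference contrast. Leave the randomised contrast unchanged.

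The cost is one sentence of analysis wording and some precision where variances are in fact equal: a CI about 2–4% wider if the reference has 57 or more PHCCs, and about 6–7% wider if it has only 24.

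Restricting the reference group to PHCCs that pass the prescribing screen is optional. It would redefine the comparator, which is a design trade-off, and it is not needed for valid standard errors once HC3 is used.
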